#### **3.2 Study Endpoints**

##### **3.2.1 Primary endpoints:**

- Incidence of solicited adverse events within 7 days after each booster vaccination.
- GMT of neutralizing antibodies against live SARS-CoV-2 virus at day 14 after each booster vaccination.

##### **3.2.2 Secondary endpoints:**

###### **1. Safety endpoints**

- Incidence of adverse reactions within 28 days after each booster dose;
- Incidence of unsolicited AE within 28 days after each booster dose;
- Incidence of serious adverse events(SAE) from the 1st booster dose to the month 6 after the 2nd booster vaccination

###### **2. Immunogenicity endpoints**

- GMT of binding antibodies against SARS-CoV-2 S and RBD protein measured by ELISA at

baseline (at day 28 post primary dose) and at day 14, 28 after the 1st booster vaccination, and at day 14 and month 6 after the 2nd booster vaccination.;

- Proportion of the participants with at least a four-fold increase of the binding antibodies against SARS-CoV-2 S and RBD protein, as compared to baseline, at day 14, 28 after the 1st booster vaccination, and at day 14 and month 6 after the 2nd booster vaccination;
- Geometric mean fold increase (GMFI) of binding antibodies against SARS-CoV-2 S and RBD protein measured by ELISA, as compared to baseline, at day 14, 28 after the 1st booster vaccination, and at day 14 and month 6 after the 2nd booster vaccination;
- GMT of neutralizing antibodies against live SARS-CoV-2 virus at 28 after the 1st booster vaccination, and at month 6 after the 2nd booster vaccination;
- Proportion of the participants with at least a four-fold increase of neutralizing antibodies against live SARS-CoV-2 virus, as compared to baseline, at day 14, 28 after the 1st booster vaccination, and at day 14 and month 6 after the 2nd booster vaccination;
- Geometric mean fold increase (GMFI) of neutralizing antibodies against live SARS-CoV-2 virus, as compared to baseline, at day 14, 28 after the 1st booster vaccination, and at day 14 and month 6 after the 2nd booster vaccination;

### **3.2.3 Exploratory endpoints:**

- Types of binding antibodies IgG against SARS-CoV-2 S protein at day 14, 28 after the 1st booster vaccination, and at day 14 and month 6 after the 2nd booster vaccination;
- Cross neutralization of the antibodies to variants of SARS-CoV-2 at day 14 after booster vaccination;
  - The specific memory immune cells, such as B cells and T cells, subgroups and germinal centers at day 14, 28 after the 1st booster vaccination, and at day 14 and month 6 after the 2nd booster vaccination.

### **3.3 Study Plan**

120 healthy subjects aged over 18 years of age who have who have received one dose of the Ad5 vectored COVID-19 vaccine in three batches consistence clinical trials will be recruited in this study. Of them, 60 subjects will be enrolled in the "0-28 days" regimen and other 60 will be enrolled in "0-56

days" regimen. Subjects in each regimen will be randomly assigned to receive the booster dose of subunit vaccine (ZF2001) against COVID-19 or a commercial influenza vaccine in a ratio of 2:1. For 0-28 days regimen and 0-56 days regimen, all participants receive a boost vaccination with ZF2001 at 4 months after the 1st boost dose.

The occurrence of adverse events within 28 days and serious adverse events within 6 months after vaccination will be observed. In addition, blood samples will be collected at baseline (at day 28 post primary dose), and at day 14, day 28 post 1st booster dose, and at day 14 and month 6 after the 2nd booster vaccination to test serum antibody levels and to profile the specific memory immune cells and antibody repertoire. Each subject will remain in this study for approximately 12 months.

In "0-28 days" regimen, participants will attend 9 visits in total, including V0 (day 28 after the prime dose, the 1st booster vaccination), V1(day 7 after 1st the booster vaccination), V2(day 14 after the 1st booster vaccination), V3(day 28 after the 1st booster vaccination), V4 (month 4 after the 1st booster vaccination, the 2nd booster vaccination), V5 (day 7 after 2nd the booster vaccination), V6 (day 14 after 2nd the booster vaccination), V7 (day 28 after 2nd the booster vaccination) and V8 (month 6 after the 2nd booster vaccination).

In "0-56 days" regimen, participants will attend 10 visits in total, including V-1(day 28 after the prime dose), V0 (day 56 after the prime dose, the 1st booster vaccination), V1(day 7 after 1st the booster vaccination), V2(day 14 after the 1st booster vaccination), V3(day 28 after the 1st booster vaccination), V4 (month 4 after the 1st booster vaccination, the 2nd booster vaccination), V5 (day 7 after 2nd the booster vaccination), V6 (day 14 after 2nd the booster vaccination), V7 (day 28 after 2nd the booster vaccination) and V8 (month 6 after the 2nd booster vaccination).

Table 1. “0-28 days” regimen subjects visit plan

| Visit No.                                          | V0*     | V1            | V2             | V3             | V4              | V5            | V6             | V7             | V8              |
|----------------------------------------------------|---------|---------------|----------------|----------------|-----------------|---------------|----------------|----------------|-----------------|
| Day/Month                                          | Day 28  | Day 35        | Day 42         | Day 56         | Day 150         | Day 157       | Day 164        | Day 178        | Day 330         |
| Visit interval                                     | V0      | V0+
7 days | V0+
14 days | V0+
28 days | V0+
4 months | V4+
7 days | V4+
14 days | V0+
28 days | V4+
6 months |
| Time window                                        | ±3 days | +3 days       | +3 days        | +3 days        | +7 days         | +3 days       | +3 days        | +3 days        | ±15 days        |
| Informed consent                                   | ●       |               |                |                | ●               |               |                |                |                 |
| Demographic information collection                 | ●       |               |                |                |                 |               |                |                |                 |
| Physical examination and preliminary screening     | ●       |               |                |                | ●               |               |                |                |                 |
| Randomization                                      | ●       |               |                |                |                 |               |                |                |                 |
| Blood collection                                   | ●(20ml) |               | ●(10ml)        | ●(20ml)        |                 |               | ●(20ml)        |                | ●(10ml)         |
| Observation for 30 min post-vaccination            | ●       |               |                |                | ●               |               |                |                |                 |
| Safety visit(AR/AE)                                | ●       | ●             | ●              | ●              | ●               | ●             | ●              | ●              | ●               |
| Report serious adverse event(SAE)※                 | ●       | ●             | ●              | ●              | ●               | ●             | ●              | ●              | ●               |
| Distribution of diary card                         | ●       |               |                |                | ●               |               |                |                |                 |
| Return of diary card and distribute a contact card |         | ●             |                |                |                 | ●             |                |                |                 |
| Return of contact card                             |         |               |                | ●              |                 |               |                | ●              |                 |

|                                                 |   |   |   |   |   |   |   |   |   |
|-------------------------------------------------|---|---|---|---|---|---|---|---|---|
| Record on the Vaccination and Visit Record Form | • | • | • | • | • | • | • | • | • |
| Record the combination drug/vaccine             | • | • | • | • | • | • | • | • | • |

\* V0 is the time for the enrollment for a booster dose.

Table 2. “0-56 days” regimen subjects visit plan

| Visit No.                                      | V-1     | V0*     | V1            | V2             | V3             | V4              | V5        | V6             | V7             | V8              |
|------------------------------------------------|---------|---------|---------------|----------------|----------------|-----------------|-----------|----------------|----------------|-----------------|
| Day/Month                                      | Day 28  | Day 56  | Day 63        | Day 70         | Day 84         | Day 180         | Day 187   | Day 194        | Day 208        | Day 360         |
| Visit interval                                 | V-1     | V0      | V0+
7 days | V0+
14 days | V0+
28 days | V0+
4 months | V4+7 days | V4+
14 days | V0+
28 days | V4+
6 months |
| Time window                                    | 0       | ±3 days | +3 days       | +3 days        | +3 days        | +7 days         | +3 days   | +3 days        | +3 days        | ±15 days        |
| Informed consent                               | •       |         |               |                |                | •               |           |                |                |                 |
| Demographic information collection             | •       |         |               |                |                |                 |           |                |                |                 |
| Physical examination and preliminary screening | •       | •       |               |                |                | •               |           |                |                |                 |
| Randomization                                  |         | •       |               |                |                |                 |           |                |                |                 |
| Blood collection                               | •(20ml) | •(10ml) |               | •(10ml)        | •(20ml)        |                 |           | •(20ml)        |                | •(10ml)         |
| Observation for 30 min post-vaccination        |         | •       |               |                |                | •               |           |                |                |                 |
| Safety visit(AR/AE)                            |         | •       | •             | •              | •              | •               | •         | •              | •              | •               |
| Report serious adverse event(SAE)※             |         | •       | •             | •              | •              | •               | •         | •              | •              | •               |

|                                                       |   |   |   |   |   |   |   |   |   |   |
|-------------------------------------------------------|---|---|---|---|---|---|---|---|---|---|
| Distribution of diary card                            |   | • |   |   |   | • |   |   |   |   |
| Return of diary card and
distribute a contact card |   |   | • |   |   |   | • |   |   |   |
| Return of contact card                                |   |   |   |   | • |   |   |   | • |   |
| Record on the Vaccination
and Visit Record Form    | • | • | • | • | • | • | • | • | • | • |
| Record the combination
drug/vaccine                |   | • | • | • | • | • | • | • | • | • |

\* V0 is the time for the enrollment for a booster dose.

### 3.4 Sample size calculation

Sample size:

Hypothesis: GMT of vaccine group is superior to that in the control group at day 28 after the booster vaccination.

The baseline GMT level before the booster immunization is expected to be about 1:20 ( $\log_{10}X=1.3$ ) after one dose of prime vaccination with Ad5 vectored COVID-19 vaccine. After the booster dose, GMT level in the vaccine group is estimated to reach 1:60 ( $\log_{10}X=1.78$ ), while the control group remains 1:20. Assume that the Standard Deviation is about 4 ( $\log_{10}X=0.6$ ), and the allocation ratio for the vaccine group and placebo group is 2:1, then the minimal sample size to provide 80% power calculated is 40 and 20, respectively.

In each regimen group, subjects are stratified to two sub-age groups: 18-59 years and 60 years or above.

Table 3. Sample size of each immunization regimen

| regimen   | Sub-age group     | sample size                |                       |
|-----------|-------------------|----------------------------|-----------------------|
|           |                   | Experimental vaccine group | Placebo control group |
| 0-28 days | 18-59 years       | 20                         | 10                    |
|           | 60 years or above | 20                         | 10                    |
| 0-56 days | 18-59 ages        | 20                         | 10                    |
|           | 60 years or above | 20                         | 10                    |
| Total     | —                 | 80                         | 40                    |

### 3.5 Randomization and blinding

#### 3.5.1 Generate random coding and distribute vaccines

The study adopts the method of stratified block randomization, and subjects will be randomly assigned by 2:1 according to age group (18-59 years old and  $\geq 60$  years old). The subjects randomization table is generated by an independent randomization professional using SAS version 9.4 or above and imported

into the Interactive Response Technology (IRT) system, accessible only to authorized personnel. Subjects, investigators and the sponsor's research management team will be blinded throughout the trial. Non-blind personnel at authorized research centers can obtain grouping information of subjects through the IRT system and use the experimental vaccine or placebo for the corresponding group based on it.

### **3.5.2 Maintenance of blinding**

Subjects, safety observers, laboratory testers will be blinded.

Those who administer, prepare and administer vaccines are unblinded staff and must sign a blinding maintenance agreements to ensure that any documents of the unblinding information are only accessible for the authorized non-blinded staff. The labels on vaccine syringe will be covered with a study number label after the preparation of the vaccine and put it ready to use.

### **3.5.3 Unblinding**

The investigators must not disrupt the blind study of the vaccine/placebo unless the study information is medically necessary for the subjects. In the event of a medical emergency, the principal investigator should be contacted as far as possible before disrupting the study vaccine/placebo blinding to discuss the need for an urgent unblinding.

Blinding will be uncover when completing the initial analysis of safety and immunogenicity 28 days after the booster dose, but the subjects and safety observers will remain blinded.

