|           | 
will be blinded throughout the trial. The unblinding staffs at authorized research centers can obtain grouping information of subjects through the IRT system and use the investigational vaccine or placebo for the corresponding group based on the grouping information.
 
The unblinding staffs are responsible to prepare and administrate the vaccine. The unblinding staffs do not allow to participate in other process of the trial.
 
Study plan:
 
120 healthy subjects aged over 18 years of age who have who have received one dose of the Ad5 vectored COVID-19 vaccine will be recruited in this study. Of them, 60 subjects will be enrolled in the "0-28 days" regimen and other 60 will be enrolled in "0-56 days" regimen. Subjects in each regimen will be randomly vaccinated with the booster dose of subunit vaccine (ZF2001) against COVID-19 or a commercial influenza vaccine in a ratio of 2:1. For 0-28 days regimen and 0-56 days regimen, all participants receive a boost vaccination with ZF2001 at 4 months after the 1st boost dose.
 
The occurrence of adverse events within 28 days post each booster vaccination, and serious adverse events within 6 months after vaccination will be observed. In addition, blood samples will be collected at baseline (at day 28 post primary dose) and at day 14, 28 after the 1st booster vaccination, and at day 14 and month 6 after the 2nd booster vaccination. For participants receiving "0-56 days" regimen, another blood sample is collected at day 0 before the 1st booster vaccination.
 
Study Duration:
 
Each subject will remain in this study for approximately 12 months from enrollment to discharge from the last visit.
 |

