### **5.7.4 Database locking**

Before statistical analysis, it is necessary to conduct a check and clean of the database. The analyzed population will be set according to the definition of the data sets, including the FAS set, PPS set and safety analysis data set, and to determine the deviation from the regimen and its impact on the analysis data set. After the database is cleaned, the database will be locked, and the statistical analysis plan is locked at the same time.

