## **5.8 Statistics Plan and Statistical Analysis**

### **5.8.1 Statistical plan**

The statistical analysis of this study will be completed in two stages. After the subjects complete the visit 28 days after the booster dose immunization, the study database will be recorded, reviewed and locked for the first stage statistical analysis.

The safety and immunogenicity data after 28 days till 6 months after immunization will be collected, reviewed and locked for the second stage statistical analysis and summary.

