## **7. Schedules**

In this study, it will take about 10 months from the preparation before initiating this study to the completion of the summary report. The schedule of clinical trial is shown as follows (for reference only):

| Implementation process of clinical trial                                    | Proposed duration |
|-----------------------------------------------------------------------------|-------------------|
| 1. Preparation before clinical trial                                        | 18 days           |
| 2. IEC Review Approval                                                      | 3 days            |
| 3. Recruitment and enrollment of the first participant                      | 1 month           |
| 4. 28-day visit after the last participant completes the last dose          |                   |
| 5. First analysis                                                           | 1 month           |
| 6. First analysis report                                                    |                   |
| 7. 6-month visit after the last participant completes the last immunization | 6 months          |
| 8. Final analysis                                                           | 1 month           |
| 9. Summary Report                                                           |                   |

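### Section 3.5.3 breaks the blind at the day-28 analysis although 3.5.1 and the abstract keep investigators and sponsor blinded throughout, and it does not say which booster sets the date

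*Protocol*

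**What the plan says.** The protocol describes the blind in four places.

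- **Section 3.5.1:** "Subjects, investigators and the sponsor's research management team will be blinded throughout the trial". The abstract says the same of these groups: they "will be blinded throughout the trial".
- **Section 3.5.2:** "Subjects, safety observers, laboratory testers will be blinded", with no end date.
- **Section 3.5.3:** "Blinding will be uncover when completing the initial analysis of safety and immunogenicity 28 days after the booster dose, but the subjects and safety observers" remain blinded. No other role is named as staying blinded.

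Two places set the timing of the first analysis.

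- **Section 5.8.1:** "After the subjects complete the visit 28 days after the booster dose immunization, the study database will be recorded, reviewed and locked" for the first-stage analysis. Like 3.5.3, it does not say which booster is meant.
- **Section 7:** the first analysis is listed after the "28-day visit after the last participant completes the last dose".

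Under section 3.1 (Stage 3), every participant receives ZF2001 four months after the first booster. Section 3.2.1 defines both primary endpoints after each booster: solicited adverse events within 7 days, and the live-virus neutralizing GMT at day 14. The second booster therefore carries primary data.

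**The concern.** For investigators and the sponsor's team, 3.5.1 and 3.5.3 give opposite instructions. Site staff, the sponsor and the laboratories could each follow a different one and believe they were complying.

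The date of the unblinding is also open. Sections 3.5.3 and 5.8.1 read as if there were one booster, and the second was added in version 1.3. Depending on which booster is meant, unblinding falls either before the second booster or after nearly all of its data are in.

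Everyone receives ZF2001 at V4, so the treatment given at that visit is no secret. The information at stake is the first-booster allocation, which still defines the randomized groups compared after the second booster. Two kinds of judgement could be affected:

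- the reading of live-virus titres, which feed a primary endpoint;
- investigators' causality calls on unsolicited and serious adverse events (5.5.4), which feed the secondary adverse-reaction endpoint (3.2.2) and those pausing and termination criteria in 3.6 that depend on association with vaccination.

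**Working it through.** No power or alpha figure is involved. The check compares the texts and then places the unblinding on the visit calendar.

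**1. Who stays blinded after the first-stage analysis**

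| Role | 3.5.1 / abstract | 3.5.2 | 3.5.3 |
|---|---|---|---|
| Subjects | throughout | yes | stay blinded |
| Safety observers | not named | yes | stay blinded |
| Investigators | throughout | not named | not kept blinded |
| Sponsor's management team | throughout | not named | not kept blinded |
| Laboratory testers | not named | yes, no end date | not mentioned |

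The investigator and sponsor rows contradict each other. The laboratory row is a gap.

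**2. Calendar** (day rows of Tables 1 and 2, days from the prime dose)

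| Regimen | V3 | V4 | V6 | V7 | V8 |
|---|---|---|---|---|---|
| 0-28 | 56 | 150 | 164 | 178 | 330 |
| 0-56 | 84 | 180 | 194 | 208 | 360 |

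The interval row prints V7 as 28 days after V0. The day row and the text of section 3.3 place it 28 days after V4, and that is used here.

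**3. Reading A: the trigger is the first booster (V3)**

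V3 to V4 is 150 − 56 = 94 days or 180 − 84 = 96 days. V3 to V6 is 164 − 56 = 108 days or 194 − 84 = 110 days.

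Unblinding day = recruitment spread + V3 day + windows + analysis time, counted from the first participant's prime dose in the first regimen primed (per regimen, in that regimen). Assumptions: a spread of 30 days (section 7 lists one month for recruitment), windows used in full (3 + 3 = 6 days), and an analysis time of 0 to 30 days (section 7 lists one month).

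- Per regimen, 0-28: 30 + 56 + 6 = 92, so day 92 to 122. The earliest V4 is 150 − 3 = 147.
- Per regimen, 0-56: 30 + 84 + 6 = 120, so day 120 to 150. The earliest V4 is 180 − 3 = 177.
- Pooled, both regimens primed together: day 120 to 150. The earliest V4 is day 147 and the earliest V6 is 164 − 3 = 161. Every day-14 sample still follows unblinding.
- Pooled, 0-56 regimen primed L days later (the protocol gives no lag; 30 to 90 days assumed): unblinding falls on day L + 120 to L + 150.

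| L | Unblinding | 0-28 V6 samples | First 0-56 V6 (L + 191) |
|---|---|---|---|
| 30 | 150–180 | 161–207 | 221 |
| 60 | 180–210 | 161–207 | 251 |
| 90 | 210–240 | 161–207 | 281 |

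The last 0-28 V6 is 30 + 164 + 13 = 207, where 13 is the V0, V4 and V6 windows (3 + 7 + 3). With a lag, some or all 0-28 V6 samples may be drawn before unblinding. The 0-56 V6 samples all follow it.

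**4. Reading B: the last dose in section 7 is the second booster**

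Unblinding follows V7 (day 178 or 208). V6 and the 7-day and 28-day safety data are then already collected, and only V8 (day 330 or 360) follows.

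**5. Which reading is likelier**

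- Section 5.6.1 labels V3 as the visit 28 days after the booster dose, and V3 is the first-booster visit.
- Section 7 adds up to (18 + 3)/30 + 1 + 1 + 6 + 1 = 9.7 months, and its text says about 10. V0 to V8 alone takes 330 − 28 = 302 or 360 − 56 = 304 days. The section leaves no room for a four-month booster interval and looks like single-booster text.

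Reading A is therefore likelier, but no sentence states it.

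**The case against.** The strongest reply is that the practical exposure is small and partly inferred. Much of it stands.

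- **Extent.** A reader might infer that all second-booster data are collected unblinded. The documents do not establish this. The trigger is not tied to a booster, the literal wording of section 7 leaves only V8 after unblinding, and staged enrolment with a pooled analysis could put some or all 0-28 V6 samples before it.
- **Laboratory testers.** A reader might infer that 3.5.3 unblinds them. It only fails to list them. Section 3.5.2 blinds them without a time limit, and nothing says that a laboratory receives the allocation.
- **Primary safety endpoint.** Counting solicited events needs no causality call. Subjects record them on diary cards (5.5.1), and subjects and safety observers stay blinded. Section 5.5.4 also treats solicited events as related by definition, although its gloss names local events. Bias here is largely contained.
- **Statistical analysis plan.** Section 5.7.4 says that "the database will be locked, and the statistical analysis plan is locked at the same time", and 5.8.1 has two locks. A reader might infer that the second-stage analysis can be settled after the first-stage result is known. The text does not support this: the first lock comes before the first-stage analysis, unblinding comes only when that analysis is complete, and nothing says that the plan is reopened.

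These replies do not resolve the conflict over investigators and the sponsor's team. Even on Reading B, those groups would know the allocation before V8, which 3.5.1 rules out.

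**Conclusion.** The contradiction is certain and rests on no assumption: sections 3.5.1 and 3.5.3 cannot both be followed for investigators and the sponsor's research management team. The omission of laboratory testers from 3.5.3 is a gap to close and does not show that they are unblinded.

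The size depends on the undefined trigger. On the likelier first-booster reading, unblinding comes before most or all second-booster data. That includes the primary day-14 titre for the 0-56 regimen in every case worked through, and for the 0-28 regimen unless the analysis is pooled and the second regimen starts later. This rests on the assumed 30-day recruitment spread, 0 to 30 days for analysis and a lag of up to 90 days. On the second-booster reading, only the month-6 visit is affected.

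The bias at stake is knowledge of the first-booster allocation when live-virus titres are read and when causality of unsolicited and serious events is judged. It should be corrected, because a primary endpoint may be read after the planned unblinding and the remedy is cheap.

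**What to change.** Reconcile the abstract and sections 3.5.1, 3.5.2, 3.5.3, 5.8.1 and 7 so that they give one rule:

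1. Name the booster whose day-28 visit triggers the first-stage analysis, and say whether that analysis is run per regimen or pooled.
2. Limit individual allocations at that point to the staff who are already unblinded and the statisticians running the first-stage analysis.
3. State that investigators who assess outcomes or causality, the sponsor's trial team and the laboratory testers stay blinded to individual first-booster allocation until the final lock after V8, along with subjects and safety observers.
4. Bring the sequence and durations in section 7 into line with the two-booster calendar.

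The cost is protocol wording. The small downside is that the trial team waits until the final lock for individual-level unblinded data.
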